**Fig. 1 Fig1:**
[figure not shown]
The order of stimulation patterns. The order of stimulation patterns of DTM or tonic is randomly assigned to two courses. One course is DTM stimulation (Stim-1), then tonic stimulation (Stim-2). The other course is in reverse order. Each stimulation pattern is performed for two days. The stimulation off period is set as one day between Stim-1 and Stim-2 (Stim-off)

After the SCS trial, the inserted leads are removed whether or not analgesic effects are obtained. In cases of an effective SCS trial or the patient agrees to implantation of an SCS system even after a non-effective SCS trial, the second step follows. With an interval of 1 month from the SCS trial, a paddle-type lead is placed on the rostral side of the SCI by laminectomy under general anesthesia (Fig. 2). The location of the lead is confirmed by intraoperative X-ray and motor-evoked potential monitoring. At the same time, an implantable pulse generator (IPG) (Intellis; Medtronic Inc.) is implanted on the hip, and it is connected to the paddle-type lead. After the SCS implantation, an effective stimulation pattern that showed efficacy in the SCS trial is started, and the analgesic effects are evaluated. In the absence of analgesic effects in the previous SCS trial, DTM stimulation is tried.

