### Secondary outcomes

The secondary outcomes are as follows: (1) evaluation of effectiveness of DTM and tonic stimulations in the SCS trial; (2) evaluation of changes of assessment scores, VAS, SF-MPQ-2, PCS, QIDS-J, and SF-36^®^, at 1, 3, 6, 12, 18, and 24 months from SCS system implantation; (3) relationship between the result of the SCS trial and the effect 3 months after SCS system implantation; (4) evaluation of preoperative factors associated with a long-term effect, defined as continuing for more than 12 months; (5) evaluation whether there is improvement of motor function using the gait function scale (FAC) at 1, 3, 6, 12, 18, and 24 months from SCS system implantation; and (6) adverse events related to this study 3 months after SCS system implantation.

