### Statistical analysis

The primary outcome will be estimated as the probability of patients achieving more than 33% pain improvement on the VAS at 3 months after SCS system implantation. The secondary outcome analyses are as follows:A logistic regression analysis using stimulation timing (Stim-1, Stim-2), stimulation pattern (tonic, DTM), pre-VAS values for each stimulation, and interaction between stimulation timing and stimulation pattern as explanatory variables. The carryover effect is examined by testing the interaction term at a significance level of 10%. If a carryover effect is observed, an additional analysis will be performed using only Stim-1.Adjusted means and 95% confidence intervals (CIs) of the rate of change or amount of change for each item (VAS, SF-MPQ-2, PCS, QIDS-J, and SF-36^®^) are calculated for each evaluation time point including pre-implantation and post 1, 3, 6, 12, 18, and 24 months using linear mixed models with time points as fixed effects. The amount of change of each item at each time point is compared after using the Dunnet-Hsu correction for multiple comparisons.For the patients undergoing implantation, logistic regression will be performed to investigate the relationship between the efficacy of the SCS trial (DTM) and the effectiveness for 33% improvement on the VAS at 3 months after implantation.Preoperative factors associated with long-term effects are examined using logistic regression analysis as explanatory variables for the following items: sex, age (<60 years vs. ≥60 years), disease duration, pain site (arm, leg, lower back, back, chest), level of SCI (cervical, thoracic, lumbar), paralysis (none, mild, moderate, severe), sensory disturbance (hypoesthesia, allodynia, numbness), and Frankel classification (B, C, D, E).Probability of gait improvement is estimated, defining an improvement as 1 point or more in the FAC category. The probability of improved cases and the 95% CIs will be calculated at each evaluation time point.

Safety analysis will be performed by tabulating the number and probability of each event.

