## Discussion

In general SCS procedures, the SCS lead is placed at the same position in the SCS trial and in SCS system implantation. The appropriate SCS lead position for achieving pain relief is the rostral side of the SCI. However, in patients with past spinal surgical histories, adhesions around past spinal surgeries make it difficult to pass the cylinder-type leads through the SCI site. On the other hand, paddle-type lead placement is more invasive than insertion of cylinder-type leads because it requires laminectomy under general anesthesia. Therefore, an SCS trial using a paddle-type lead is not reasonable. In this study protocol, the SCS trial is planned using cylinder-type leads placed on the caudal side of the SCI. The SCS lead positions are not theoretically appropriate on that side and may not show sufficient pain relief effects. The reasons for performing this SCS trial are as follows. The first reason is to avoid the risk of bleeding or tissue damage by passing the cylinder-type leads through the SCI site. The second reason is to assess whether the result of the SCS trial with caudal stimulation of the SCI is a predictor of the long-term effects of SCS implantation with rostral stimulation of the SCI. The last reason is to provide patients time to decide on permanent SCS system implantation.

The cutoff line for determining whether a treatment is a success or not is important. The 30% to 40% range in pain reduction is widely used as a standard for clinically significant improvement. Hanley et al analyzed the relationship of pain intensity and meaningful change in pain for chronic pain after SCI and amputations [37]. They concluded that a 33% decrease in pain was a reasonable standard for meaningful change for chronic pain after SCI, and 30% may be low. Based on the report, the cutoff line for the primary outcome is set as more than 33% improvement in pain relief in this study. In assessing the effects of multiple stimulation patterns during an SCS trial, there are two main biases. One is the order of stimulation, and the other is the residual effect of previous stimulation. To reduce the former bias, the SCS trial is randomly assigned as DTM and tonic stimulation, followed by their crossover. To reduce the latter bias, a 1-day off period after a previous stimulation is set to wash out the residual effect.

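### The analysis of the SCS trial as a predictor uses only the DTM result, although patients may be implanted on tonic, and no listed analysis takes up the long-term prediction named in the Discussion

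*Protocol article*

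**What the plan says.** The Secondary outcomes section of the protocol article lists as item (3) the "relationship between the result of the SCS trial and the effect 3 months after SCS system implantation". The abstract gives the same item in the same unrestricted form. The Statistical analysis section, which limits this analysis to implanted patients, states: "logistic regression will be performed to investigate the relationship between the efficacy of the SCS trial (DTM) and the effectiveness for 33% improvement". The outcome there is VAS improvement assessed at month 3.

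Under Study procedures, each patient receives both DTM and tonic in randomised order during the SCS trial. The text after Figure 1 then says: "After the SCS implantation, an effective stimulation pattern that showed efficacy in the SCS trial is started, and the analgesic effects are evaluated". If the SCS trial gave no analgesia and the patient still agrees to implantation, DTM is tried.

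The Discussion gives three reasons for running the SCS trial with caudal leads. The second concerns the question "whether the result of the SCS trial with caudal stimulation of the SCI is a predictor of the long-term effects of SCS implantation". The Secondary outcomes section speaks of "a long-term effect, defined as continuing for more than 12 months". The regression for that long-term effect lists sex, age, disease duration, pain site, level of injury, paralysis, sensory disturbance and Frankel grade. The SCS-trial result is not in the list.

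**The concern.** There are two separate mismatches.

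- **Predictor.** The outcome list asks about the SCS-trial result as a whole, while the analysis uses only its DTM half. A tonic-only responder has an effective SCS trial by the study's own procedure and is started on tonic. The model nevertheless relates that patient's 3-month outcome to the response to a pattern with which the patient was not started. Pooling such patients with those who responded to neither pattern makes the SCS trial look less predictive than it may be.
- **Time horizon.** The article concedes that the caudal lead position is theoretically unsuitable and offers long-term prediction as one reason for the step. No listed analysis relates the SCS-trial result to any outcome beyond 3 months, although VAS is assessed to 24 months. At the end of the study that question would have no planned answer.

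**Working it through.** **The plan's own figure.** The sample size is 10, set by feasibility. At 2 to 4 eligible patients a year, 10 patients take 10/4 = 2.5 to 10/2 = 5 years, and 3 to 5 years yield 2×3 = 6 to 4×5 = 20 patients. The figure is consistent with its inputs. It means that at most 10 patients enter the predictor analysis.

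**Where each type of patient falls.**

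| SCS-trial response | Pattern started after implantation | SCS trial effective? | DTM result |
|---|---|---|---|
| DTM only | DTM | yes | good |
| Both | an effective one | yes | good |
| Tonic only | tonic | yes | poor |
| Neither | DTM | no | poor |

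The last two columns disagree only for tonic-only responders. With a yes/no predictor, coding by the pattern carried forward and coding by response to either pattern give the same grouping.

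**Illustration 1 (all counts assumed; the article gives none).** Of 10 implanted patients, let 3 of 4 DTM responders, 2 of 3 tonic-only responders and 1 of 3 with no response succeed at 3 months.

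- DTM-only coding: 3/4 against (2+1)/(3+3) = 3/6; OR = (3×3)/(1×3) = 3.
- Pattern carried forward: (3+2)/(4+3) = 5/7 against 1/3; OR = (5×2)/(2×1) = 5.

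**Illustration 2 (assumed success rates).** Take 5 responders to any pattern with success rate a and 5 non-responders with rate b. If k of the 5 responders are tonic-only, the DTM-only reference group has rate r = (k·a + 5·b)/(k + 5), and OR = [a/(1−a)] / [r/(1−r)].

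| k | r (a = 70%, b = 30%) | OR | r (a = 80%, b = 20%) | OR |
|---|---|---|---|---|
| 0 | 30% | 5.44 | 20% | 16.0 |
| 1 | 2.2/6 = 36.7% | 4.03 | 1.8/6 = 30% | 9.33 |
| 2 | 2.9/7 = 41.4% | 3.30 | 2.6/7 = 37.1% | 6.77 |
| 3 | 3.6/8 = 45% | 2.85 | 3.4/8 = 42.5% | 5.41 |

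The odds ratio moves toward 1 as k rises, and the two codings agree at k = 0.

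**Whether ordinary logistic regression can be fitted.** With a yes/no predictor there is no finite estimate if all or none succeed in either group. For a 5 v 5 split at 70% and 30%, each group is all-or-none with probability 0.7⁵ + 0.3⁵ = 0.1705, so the chance is 1 − (1 − 0.1705)² = 0.312. Over splits of 5 v 5, 4 v 6 and 3 v 7, and both pairs of rates, it ranges from 0.312 to 0.621. This supports exact, descriptive reporting; it is not part of either mismatch.

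**Long-term question.** The predictor analysis has the SCS-trial result but ends at 3 months. The long-term regression goes beyond 12 months but lacks the SCS-trial result. None of the other listed analyses contains both.

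**The case against.** DTM is the focus of the study hypothesis and the default after a non-effective SCS trial, so asking whether caudal DTM response predicts success is a reasonable question. That stands as a reason to keep a DTM-specific analysis. It does not settle the mismatch, because the analysis covers all implanted patients, including those started on tonic, and the declared outcome is not limited to DTM.

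Three stronger readings are tempting and are not supported.

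- A reader might infer that tonic-only responders are coded as trial failures. The article does not say whether SCS-trial efficacy enters as yes/no or as a continuous value. What can be said is that they enter with a low DTM value, or as DTM non-responders if the coding is binary.
- A reader might infer that the association could be reversed. Where DTM responders do at least as well as patients with no response, that would need tonic-only responders to do better after implantation than DTM responders. Nothing in the article suggests this.
- A reader might infer that a declared outcome goes unanalysed. The 3-month horizon matches secondary outcome (3). The long-term conflict is only with the Discussion's rationale, and the other two reasons given there do not depend on it.

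It is also fair that the number of tonic-only responders is unknown, and that with at most 10 patients the gap between odds ratios of 3 and 5 lies well within sampling error. The restriction to implanted patients is already stated and needs no change.

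**Conclusion.** The point holds as two inconsistencies in secondary analyses of an exploratory study. The predictor is narrower than the declared outcome and does not match the treatment started in tonic-only responders. The expected consequence is attenuation: from 5 to 3 in the first illustration, and from 5.44 to between 4.03 and 2.85, or from 16.0 to between 9.33 and 5.41, in the second. These sizes rest wholly on assumed rates, on yes/no coding, and on 1 to 3 tonic-only responders among 10 patients; with none the effect is nil. The long-term prediction offered in the Discussion has no listed analysis. The primary outcome, the randomisation and the safety analysis are unaffected. The change is worth making because it is nearly free and the question helps to justify an invasive step.

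**What to change.** In the Statistical analysis section:

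1. Define the predictor in the third secondary analysis as SCS-trial response to the pattern carried into implantation, or to either pattern, and state how response is coded. Keep DTM-only response as a secondary cut.
2. Cross-tabulate the SCS-trial result descriptively, with exact confidence intervals, against the 3-month outcome and against the effect lasting more than 12 months.
3. If the long-term table is not wanted, withdraw long-term prediction as a reason for the SCS trial in the Discussion.

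The cost is a change of wording and slightly more descriptive output. All the data are already to be collected, and the result remains exploratory either way.

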### Clinical assessments

At entry, clinical research physicians obtain information from patients regarding age, sex, past history, medications, cause of SCI (traumatic or non-traumatic), level of SCI (cervical, thoracic, lumbar), location of pain (arm, leg, lower back, back, chest), degree of paralysis (none, mild, moderate, severe), sensory disturbance (hypoesthesia, allodynia, numbness), duration of disease, and Frankel grade (B-E). During the SCS trial, the degree of pain is evaluated using a VAS according to the plan (Table 1). After SCS system implantation, assessment items are evaluated according to the plan, including degree of improvement of pain relief, mental health, comprehensive health, and gait function (Table 1). Six months after SCS system implantation, if no improvement of any of the assessment items is seen, removal of the implanted SCS system would be considered.

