### Primary outcome

Pain improvement is defined as more than a 33% reduction in the VAS score. The primary outcome is rates of achieving pain improvement at 3 months after SCS system implantation.

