### Sample size

There is no reference clinical data for the efficacy of DTM stimulation using a paddle-type lead placed on the rostral side of the SCI because there is only one case report [26]. Therefore, the sample size is not able to determine on statistical assumptions. Assume that there are 2 to 4 cases who meet the inclusion criteria of this study in a year. The sample size is set 10 as the number that can be achieved in 3 to 5 years.

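### Secondary analysis 3 relates the SCS trial (DTM) result to the implant result through a yes/no 33% VAS cut in at most 10 patients; the VAS is scored at both steps, and using its full scale would keep more information and give a finite estimate.

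*Protocol article*

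**What the plan says.** Secondary outcome (3) in the Protocol article is the "relationship between the result of the SCS trial and the effect 3 months after SCS system implantation". The Statistical analysis section turns this into a model: "For the patients undergoing implantation, logistic regression will be performed", to study the "relationship between the efficacy of the SCS trial (DTM) and the effectiveness for 33% improvement on the VAS at 3 months after implantation". The outcome is therefore binary, and the Primary outcome section fixes its threshold: "Pain improvement is defined as more than a 33% reduction in the VAS score".

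The number of patients is small. Under Sample size: "The sample size is set 10 as the number that can be achieved in 3 to 5 years". Ten is a ceiling for this analysis, because implantation is conditional (Study procedures, text after Fig. 1): "In cases of an effective SCS trial or the patient agrees to implantation of an SCS system even after a non-effective SCS trial, the second" stage, implantation, is carried out. Missing values are not to be compensated for.

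The continuous data exist. Clinical assessments states: "During the SCS trial, the degree of pain is evaluated using a VAS according to the plan (Table 1"). Secondary outcome (2) lists the VAS at 3 months after implantation.

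The Discussion gives three reasons for doing the caudal SCS trial. One is to "assess whether the result of the SCS trial with caudal stimulation of the SCI is a predictor of the long-term effects".

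**The concern.** The question is one of association between two quantities, each measured as a change in VAS. The Discussion defends the 33% cut as a standard for meaningful change in pain and applies it to the primary outcome. That is a sound reason to report responders. It is not a reason to measure association on a yes/no scale, where a 34% and a 90% reduction count the same and a 32% and a 34% reduction count as opposites.

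With 10 patients or fewer there are two costs. Power falls, and the logistic model may have no finite odds ratio, because an empty cell (binary predictor) or complete separation (continuous predictor) sends the estimate to infinity. The trial could then say little about whether the SCS trial predicts the implant result, although the data collected could say more.

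**Working it through.** **The plan's own figure.** The sample size of 10 comes from accrual, not power. At 2 eligible cases a year, 10/2 = 5.0 years; at 3 a year, 10/3 = 3.3 years; at 4 a year, 10/4 = 2.5 years. This agrees roughly with the stated 3 to 5 years. No power or significance level is given for this analysis.

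**Inputs from the article:** at most 10 implanted patients; binary 33% outcome; VAS scored at both steps.

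**Assumptions, not from the article:** VAS reductions in the SCS trial and at 3 months are bivariate normal with correlation r; 50% respond at each step; two-sided 5%.

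**Information lost, by formula.** Cutting one normal variable at its median multiplies the correlation by √(2/π) = 0.798. Cutting both gives (2/π)·arcsin(r).
- r = 0.7: 0.7 × 0.798 = 0.56 with one cut; 0.637 × 0.775 = 0.49 with both.
- r = 0.8: 0.8 × 0.798 = 0.64 with one cut; 0.637 × 0.927 = 0.59 with both.

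**Power at n = 10, by simulation:**

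| Analysis | r = 0.7 | r = 0.8 |
|---|---|---|
| Both continuous, Pearson | 68% | 87% |
| Both continuous, Spearman | 56% | 75% |
| Only the outcome cut | 43% | 59% |
| Both cut, Fisher exact | 21% | 32% |

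Separate runs agree within a few points (Spearman up to 58% and 79%).

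**Check on Pearson** by Fisher's z, power ≈ Φ(atanh(r)·√(n−3) − 1.96):
- r = 0.7: 0.867 × 2.646 = 2.29; Φ(0.33) = 63%.
- r = 0.8: 1.099 × 2.646 = 2.91; Φ(0.95) = 83%.

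The approximation is slightly low but confirms the scale.

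**Check on the outcome-only cut with logistic models.** A likelihood-ratio test calibrated to 5% gives 42% and 57%. The uncalibrated test gives 57% and 74%, but its type I error is about 8%. The Wald test never reached significance; the largest |z| seen was 1.86. The article does not say which test would be used.

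**Why the both-cut version is so weak.** With 5/5 splits on both variables, a perfect table has Fisher p = 2/252 = 0.008. Moving one patient on each side (4,1 / 1,4) gives p = 52/252 = 0.21. Only the perfect table is significant. With 70% response and 30% SCS-trial success, power is 3% at either correlation.

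**How often no finite estimate exists (n = 10):**
- Binary predictor, empty cell: 48% of trials at r = 0.7, 57% at r = 0.8.
- Continuous predictor, complete separation: 19% and 28%.

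**Fewer implanted, r = 0.7:**
- n = 8: Pearson 55%, Spearman 42% (up to 46% in other runs), calibrated likelihood ratio 31%, Fisher 8%.
- n = 6: Pearson 38%, calibrated likelihood ratio 12%, Fisher 0%.

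**The case against.** **The predictor's form is not stated.** The article does not say that the SCS-trial result enters as yes/no. The effective/non-effective wording describes who proceeds to implantation, not how a covariate is coded, and coding is commonly left to the full protocol or SAP. This stands. A reader might infer that the analysis is a 2×2 table; the text does not fix that, so the 21% and the empty-cell figures are conditional. The cut of the outcome is fixed, and its cost remains.

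**A strong relationship would not always be missed.** A reader might infer that it usually would be. With only the outcome cut, power at correlation 0.8 is about 59%, more than half, so that inference fails. It holds at 0.7, or for a binary predictor or a Wald test.

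**The alternative is also limited.** This stands too. Ten patients is the main constraint. Spearman's advantage over the outcome-only cut is only 6 to 7 points at n = 10 and correlation 0.5. If reductions are bounded at 0 to 100% (assumed means 15% and 33%, SD 30), Pearson at 0.7 falls to 62% for n = 10 and 49% for n = 8.

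**The trial is exploratory, and 33% is clinically grounded.** Both are true, and no passage plans to read a null result as absence of prediction. But an exploratory analysis needs an interpretable estimate most of all, and the responder view can be kept as description.

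**Conclusion.** The concern holds as a matter of efficiency and estimability in one secondary analysis; no stated figure is wrong and the primary outcome is untouched. With 10 implanted and correlation 0.7, moving to the full scale raises power from about 43% to about 68% (Pearson), or 56% (Spearman), if only the outcome is cut. If both are cut, it starts from about 21% or less. It also avoids an infinite odds ratio, expected in roughly a fifth of trials with a continuous predictor and half with a binary one. These sizes rest on assumed correlations, near-normal VAS reductions, 50% response and a 5% level. That no continuous version of this analysis is planned can be said only of the article, since the full protocol and SAP are not shown.

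**What to change.** In the Statistical analysis section, make the main analysis of secondary outcome (3) a linear regression, or Pearson correlation, of percent VAS reduction at 3 months on percent VAS reduction during the DTM period of the SCS trial. Tying the predictor to DTM matches the article's own wording. Report the slope or correlation with its 95% CI and a scatter plot marking the 33% lines. Give Spearman as a sensitivity analysis, and keep the 33% responder cross-table as description.

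The cost is a change of wording; the VAS scores are already planned. The downside is that a slope or correlation replaces the odds ratio, and one outlier can influence it at this sample size. The plot and the rank analysis would show that.

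### The logistic regressions for secondary outcomes 3 and 4 do not fit a trial of at most 10 patients: the factor model needs 17 coefficients if entered jointly and would usually break down even one multi-category factor at a time

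*Protocol article*

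**What the plan says.** All references are to the Protocol article.

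- **Statistical analysis, secondary outcome 4:** "Preoperative factors associated with long-term effects are examined using logistic regression analysis as explanatory variables for the following items". The items begin with "sex, age (<60 years vs. ≥60 years), disease duration", then "pain site (arm, leg, lower back, back, chest") and "level of SCI (cervical, thoracic, lumbar"). Paralysis (four grades), sensory disturbance (three types) and Frankel class (B to E) follow. The text does not say whether the items enter together or singly, and it mentions no reduction or penalisation.
- **Statistical analysis, secondary outcome 3:** "For the patients undergoing implantation, logistic regression will be performed to investigate the relationship between the efficacy of the SCS trial (DTM") and the 33% VAS improvement at 3 months.
- **Sample size:** "Therefore, the sample size is not able to determine on statistical assumptions". The number is set by feasibility: "Assume that there are 2 to 4 cases who meet the inclusion criteria of this study in a year", and "The sample size is set 10 as the number that can be achieved in 3 to 5 years".
- **Ten is a ceiling.** Under Study procedures, implantation follows an effective trial or the patient's agreement after a non-effective one. The section on missing data says that no statistical method will compensate for it.

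**The concern.** A logistic model with more parameters than patients cannot be identified. One with a multi-level factor and very few patients per level tends to separate: some level contains only responders or only non-responders, and its odds ratio runs to zero or infinity. Standard software then stops, drops terms, or prints very large estimates with meaningless standard errors.

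Two declared secondary questions depend on these models: which preoperative factors go with benefit beyond 12 months, and whether the caudal trial result relates to benefit after rostral implantation. The second carries extra weight. The Discussion gives prediction of the implant's long-term effect as one of three reasons for performing the caudal trial, and this regression is the only listed analysis relating trial result to implant outcome. The risk is that neither question gets a usable answer, or that unstable odds ratios are read as prognostic findings.

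**Working it through.** **1. The plan's own figure.** At 2 eligible patients per year, 2 × 5 years = 10. At 4 per year, 4 × 3 years = 12, or 10/4 = 2.5 years to reach 10. N = 10 is consistent with the stated accrual. There is no power calculation to reproduce.

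**2. Outcome 4, joint model.** Coefficients are (levels − 1) per categorical item. Disease duration has no printed categories and is taken as one linear term.

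| Item | Levels | Coefficients |
|---|---|---|
| Sex | 2 | 1 |
| Age group | 2 | 1 |
| Disease duration | linear | 1 |
| Pain site | 5 | 4 |
| Level of SCI | 3 | 2 |
| Paralysis | 4 | 3 |
| Sensory disturbance | 3 | 2 |
| Frankel class | 4 | 3 |
| **Total** | | **17** |

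With the intercept there are 18 parameters. Ten patients give a design matrix of rank at most 10, so at most 9 coefficients beyond the intercept. Other codings do not help:

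- Paralysis and Frankel class as linear scores: 17 − 2 − 2 = 13.
- Several pain sites and sensory types allowed per patient: 17 + 1 + 1 = 19.
- Both changes: 15.

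In 2,000 simulated designs with n = 10 the rank was always 10. All 1,000 simulated data sets were completely or quasi-completely separated.

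**3. Outcome 4, one factor at a time.** Assumptions: n = 10, k equally likely categories, and the same response probability p in each. A fit has a non-finite coefficient when any occupied category is all responders or all non-responders. Over category counts n₁,…,n_k from a multinomial(10; 1/k):

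P(fail) = 1 − Σ P(n₁,…,n_k) × Π over n_j > 0 of [1 − p^n_j − (1 − p)^n_j]

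| Levels | Items | p = 50% | p = 30% or 70% |
|---|---|---|---|
| 2 | sex, age group | 21.7% | 38.7% |
| 3 | SCI level, sensory disturbance | 68.8% | 80.0% |
| 4 | paralysis, Frankel class | 90.6% | 94.4% |
| 5 | pain site | 96.7% | 98.2% |

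**4. Outcome 3.** Assumptions: trial efficacy coded yes/no, trial success 40–60%, and 3-month response 30–80% in each group. The four cells then have probabilities q₁ to q₄, and the log odds ratio is finite only if no cell is empty. By inclusion–exclusion:

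P(empty) = Σ(1 − q_i)ⁿ − Σ(1 − q_i − q_j)ⁿ + Σ q_iⁿ

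- Lowest at n = 10 (all rates 50%, each q = 0.25): 4(0.75¹⁰) − 6(0.50¹⁰) + 4(0.25¹⁰) = 0.219.
- Highest at n = 10 (trial success 60%, response 80% in both groups; q = 0.48, 0.12, 0.32, 0.08): 0.7355 − 0.1168 + 0.0007 = 0.619.

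| n | Range of P(empty cell) |
|---|---|
| 10 | 22–62% |
| 8 | 38–73% |
| 6 | 62–85% |

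**5. Best finite result for outcome 3.** Among all n = 10 tables without an empty cell, the smallest two-sided Wald p comes from cells 1, 4, 4, 1: |ln(1/16)| / √(1 + 1/4 + 1/4 + 1) = 2.773/1.581 = 1.754, so p = 0.080. No yes/no table of this size gives both a finite odds ratio and Wald p < 0.05.

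**The case against.** The strongest reply is that the text never calls the factor model multivariable. Examining candidates one by one fits its words. Coding, collapsing of sparse levels, and exact or penalised likelihood are commonly settled in an analysis plan that is not shown here, and Firth or exact fits are still logistic regression. This stands in part. A reader might infer that the factor regression is impossible however it is run; the documents do not support that. On the single-factor reading, sex and age group would more often than not give a finite estimate, and disease duration may be one linear term. The reply does not rescue the five items with three or more levels, for which ordinary logistic regression would usually break down.

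A reader might also infer that the outcome 3 regression fails to the same degree. It does not. It has one predictor, the yes/no coding is an assumption, and the trial stage is measured by VAS, so the predictor could be a continuous change. The empty-cell figures would then not apply, although separation would remain possible.

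Finally, the trial is declared exploratory and its size is openly a matter of feasibility. Neither analysis carries a stated significance test or decision rule, and nothing says that the factors will be used to select patients. That lowers the severity but does not make the models estimable. The age cut at 60 is pre-specified, costs one coefficient and is not part of this point.

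**Conclusion.** The point holds at moderate severity.

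- **Joint reading of outcome 4:** failure is certain. There are 18 parameters against at most 10 patients, and at least 13 coefficients under every coding tried, against the 9 available.
- **Single-factor reading of outcome 4:** failure is usual for the multi-category items (about 69–98%) and a minority risk for the 2-level items (22–39%). These figures assume equal category frequencies and 30–70% response.
- **Outcome 3:** a small-sample weakness, with a 22–62% chance of no finite odds ratio at n = 10 and more with fewer implanted patients. This depends on yes/no coding and on assumed response rates, because the Sample size section says that no reference data exist.

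A reader might infer that the trial's main result is compromised. It is not: the primary outcome is a single proportion and does not depend on these models.

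**What to change.** **Outcome 4.** Replace the logistic model with a table of each factor by long-term effect (yes/no). For a short list of factors named in advance, add single-factor exact or Firth-penalised fits, with paralysis and Frankel class entered as ordinal scores. Label the results hypothesis-generating.

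**Outcome 3.** Report the 2×2 table of DTM trial result by 3-month response, with exact confidence intervals for positive and negative predictive value. Add the Spearman correlation between percent VAS reduction in the DTM trial period and percent VAS reduction at 3 months. Exact methods also cope with the tables that defeat the regression: a split of 5/0 against 0/5 has no finite odds ratio, but Fisher's exact p is 0.008.

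**Cost.** Analysis wording only. Data collection, sample size and patient procedures do not change. The price is that the claims for both outcomes become descriptive, which is what 10 patients can support.
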